| OBJECTIVES                | 
Main objectives:
 
 
- To estimate the effect of an 18-month meditation intervention on the volume and perfusion of the anterior cingulate cortex in comparison to an absence of intervention (passive control);
 
- To estimate the effect of an 18-month meditation intervention on the volume and perfusion of the insula compared to a 18-month language learning intervention.
 
 
Secondary objectives:
 
 
o Related to interventions:           
 
- To compare the effects of the two interventions (meditation and learning a foreign language, for 18 months) with each other and with a passive control in non-meditating seniors, on behavioural and biological measurements (cognitive, psycho-affective, blood, sleep, and imaging), including measurements to assess potential deleterious effects as well as gender-specific effects (male/female);
 
- To estimate the maintenance of the interventions' effects (meditation and learning a foreign language in the long term, 35 months after the end of the intervention) on cognition, psycho-emotional factors, sleep and lifestyle (but also imaging and blood markers if budget allows).
 
- To compare the long-term effects (35 months after the end of the intervention) of the 2 interventions (meditation and learning a foreign language) on cognition, psycho-emotional factors,
 
 
 
 |

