#### Secondary objectives

○ In relation to the interventions studied:

OBJECTIVE 2: To compare the effect of an 18-month mindfulness-based intervention, an 18-month intervention based on language learning and no intervention, on areas of cognition, psycho-affective/emotion, compassion, support, mindfulness, sleep, wellbeing, quality of life, and on biological and radiological measures, including sex-specific effects;

OBJECTIVE 2bis: To estimate the maintenance of the effects of the interventions (mindfulness-based training and language learning) 29 mois +/- 6 mois months after the end of the intervention on areas of cognition, psycho-affective/emotion, compassion, support, mindfulness, sleep, wellbeing, quality of life (and on biological and radiological measures depending on budget availability);

OBJECTIVE 2ter: To compare the long-term effects (29 mois +/- 6 mois months after the end of the intervention) of the two interventions (the 18-month mindfulness-based intervention and the 18-month intervention based on language learning) on areas of cognition, psycho-affective/emotion, compassion, support, mindfulness, sleep, wellbeing, quality of life (and on biological and radiological measures depending on budget availability);

OBJECTIVE 3: To compare the effect of an 18-month mindfulness-based intervention and of an 18-month intervention based on language learning vs. no intervention on participants' partners (perception of participant's changes, interactions with the participant, willingness to help the participant).

OBJECTIVE 3bis: To estimate the effects of the interventions (meditation and foreign language learning) on participants' partners (perception of participant's changes, interactions with the participant, willingness to help the participant) 21 months after the end of the intervention.

OBJECTIVE 3TER: To estimate the effects of the interventions (meditation and foreign language learning, during 18 months) (acceptance of the interventions, perception of changes...).

○ Without relation to the interventions studied:

OBJECTIVE 4: To estimate the association between meditation practice and behavioral and biological measures (cognition, psycho-affective, lifestyle, blood, sleep and radiological measures), by comparing expert meditators and participants with no previous meditation practice;

OBJECTIVE 5: To identify neural signatures of mindfulness and compassion meditations in senior expert meditators;

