### **Secondary outcomes**

#### **Behavioral outcomes (OBJECTIVES 2, 4, 6, 7 and 9):**

The main behavioural outcome will correspond to the comparison between meditation intervention and language learning intervention on the global metacognitive composite score, consisting in the mean of the attentional, constructive and deconstructive subscores as defined in (Dahl et al., 2015) and updated in (Schlosser et al., Submitted); see Section “*Analysis of trial objectives*” below for further details about this score.

Additional composite scores will be computed as z-scores measured from the neuropsychological tests and/or the questionnaires. Composite scores will correspond to the mean of z-scores calculated from all the cognitive scores obtained for the corresponding cognitive function that will have a normal distribution and will not have floor or ceiling effect. Additional exploratory analyses will be conducted on all individual behavioural measures obtained.

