## Type I error rate

For the main secondary outcome, the main effect (of the meditation intervention compared to the English intervention) on the global metacognitive composite score will be tested with a two-sided type I error rate  $\alpha=5\%$ ; if significant, the main effect on each of the 3 composite subscores (attentional, constructive and deconstructive) will be tested with a Bonferroni correction ( $\alpha=5/3\%=0.0166\%$ ) to strictly control for type I error inflation.

The evolution of the same scores in the passive control group will be provided for the sake of description.

Each statistical test for the other secondary endpoints will be performed with a two-sided type I error rate  $\alpha=5\%$ .

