#### Secondary objectives

##### *Objective 2 (WP 1 to 6)*

For the main secondary outcome, the difference between the inclusion and 18 months of i) the global metacognitive composite score, and ii) the attentional, constructive and deconstructive subscores, will be compared between the meditation intervention and language learning intervention groups.

These scores will be computed as described in (Schlosser et al., Submitted). Briefly, the metacognitive composite score drew from the following self-report measures employed in the Age-Well randomised controlled trial (See Poisnel et al. for details and corresponding references): the Compassionate Love Scale (CLS; stranger-humanity version), the Drexel Defusion Scale (DDS), the Five Facet Mindfulness Questionnaire (FFMQ), the Interpersonal Reactivity Index (IRI), the Multidimensional Assessment of Interoceptive Awareness Version 2 (MAIA-2), and the Prosocialness Scale. Amongst those, seven subscales were judged to primarily capture attentional aspects: noticing (MAIA subscale), attention regulation (MAIA), emotional awareness (MAIA), self-regulation (MAIA), body listening (MAIA), observing (FFMQ), and acting with awareness (FFMQ). Four (sub)scales were judged to primarily capture constructive aspects: the CLS, empathic concern (IRI subscale), perspective taking (IRI), and the Prosocialness Scale. Another four scales were judged to primarily capture deconstructive aspects: the DDS, non-judging (FFMQ), non-reactivity (FFMQ), distress (IRI).

To compute each composite score, scale scores will be first standardised using their baseline mean and standard deviation, and the sum of the standardised scale scores will then be divided by the number of scales included in the respective composite. Scales will be reverse-scored if higher total scores reflect worse functioning. Ergo, higher composite scores will indicate higher capacities in the psychological processes characterising the three meditation families. Participants with missing scale scores will not be included in the composite score to which this scale is assigned.

The evolution of the same scores in the passive control group will be provided for the sake of description. Moreover, the difference between the inclusion and 18 months of all additional composite scores and individual behavioural cognitive, psychoaffectives, life, blood, sleep and imaging measures will be compared between

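### The main secondary outcome, the global metacognitive composite, has no planned between-arm comparison with passive control, although Objective 2 calls for one

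*Combined protocol and SAP*

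**What the plan says.** The protocol states Objective 2 in the Summary of the research and again in section 2.2.1. The interventions are to be compared "with each other and with a passive control in non-meditating seniors, on behavioural and biological measurements". The secondary SAP restates this as a three-arm objective: "To compare the effect of an 18-month mindfulness-based intervention, an 18-month intervention based on language learning and no intervention, on areas of cognition".

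The same SAP then narrows the comparison for its leading outcome:

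- Behavioral outcomes: "The main behavioural outcome will correspond to the comparison between meditation intervention and language learning intervention on the global metacognitive composite score".
- Type I error rate: "the main effect (of the meditation intervention compared to the English intervention) on the global metacognitive composite score will be tested", two-sided at 5%. If that is significant, "the main effect on each of the 3 composite subscores (attentional, constructive and deconstructive) will be tested with a Bonferroni correction".
- Objective 2 (WP 1 to 6): the 18-month change in the global score and its three subscores "will be compared between the meditation intervention and language learning intervention groups".
- Passive arm, in both of the last two sections: "The evolution of the same scores in the passive control group will be provided for the sake of description".

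A three-group comparison is planned, but for a different set of variables: "the difference between the inclusion and 18 months of all additional composite scores and individual behavioural cognitive, psychoaffectives, life, blood, sleep and imaging measures".

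**The concern.** The objective implies three pairwise contrasts, and the main secondary outcome receives one. The two that use the passive arm, a third of the randomised participants, are absent for the global score and its subscores.

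The protocol gives the two comparators different jobs. The opening of section 2 uses the language arm to isolate what is specific to meditation and the passive arm to capture the non-specific effect. Section 1 also says that a benefit can be expected from language learning itself, so English is not an inert comparator. A null meditation–English result is then compatible with both arms improving or with neither improving. A positive result is compatible with a meditation gain or an English loss. The part of Objective 2 that asks about no intervention has no planned inferential answer on this score.

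**Working it through.** **1. Contrasts promised and planned, for the global composite**

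| Contrast | Objective 2 | Secondary SAP |
|---|---|---|
| Meditation vs English | yes | tested, two-sided 5% |
| Meditation vs passive | yes | no test, no difference estimated |
| English vs passive | yes | no test, no difference estimated |

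So 0 of the 2 contrasts with passive are planned. The three-group sentence covers the additional composites and the individual measures. The general 5% rule is for the other secondary endpoints. Neither takes in this score.

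**2. The plan's own figure.** The only sample size in the plan for the randomised comparison is for the primary endpoints: effect size 0.75, two-sided 1.25%, 80% power, 42 per arm. A two-sample t-test gives n = 41.24, rounded up to 42, so the figure reproduces. No size or power is stated for the composite.

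**3. Inputs for the illustration.** There are 50 per arm (secondary SAP, Sample size: 42 + 8). The lower value of 45 per arm comes from the 135 seniors in the Lockdown annex, 135/3, assuming balance. The test is an unadjusted two-sample t-test at two-sided 5%, with no missing data. Effects are in SD of the 18-month change relative to passive and are assumed: meditation +0.5; English +0.3, +0.1 or 0.

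**4. Power.** The noncentrality is d × √(n/2), where d is the difference between the two arms compared. At n = 50, √(50/2) = 5.

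| Contrast | d | Noncentrality (n = 50) | Power, n = 50 | Power, n = 45 |
|---|---|---|---|---|
| Med vs English, English +0.3 | 0.2 | 1.0 | 17% | 15% |
| Med vs English, English +0.1 | 0.4 | 2.0 | 51% | 47% |
| Med vs English, English 0 | 0.5 | 2.5 | 70% | 65% |
| Med vs passive, any English effect | 0.5 | 2.5 | 70% | 65% |

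The two contrasts see the same difference only if English has no effect.

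**5. Can the trial support the added contrasts?** At 50 per arm the difference detectable with 80% power is 0.57 SD at 5% and 0.63 SD at 2.5%, the stricter Holm step for two tests. Power for 0.5 SD at 2.5% is 59%.

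**6. What description alone provides.** A within-arm mean change has a 95% half-width of 1.96/√50 = 0.28 SD. A between-arm difference would have 1.96 × √(2/50) = 0.39 SD. The plan provides the first kind of interval and not the second.

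**7. Multiplicity.** All three pairwise contrasts at an unadjusted 5% give a family-wise error of about 12.2% (simulation under the global null), so added tests need a rule.

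**The case against.** The strongest reply is that the choice is deliberate and sound. The composite is built from self-report scales and participants know their arm, so an active comparator is the better guard against expectation effects. It mirrors Objective 1bis, and a single gated hierarchy is easy to defend. That stands, and nothing here argues for demoting meditation versus English.

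Second, Objective 2 covers broad domains and does not promise every contrast on every score. The scales that feed the composite are themselves individual measures, so they fall under the three-group comparison. This limits the gap to one global score and three subscores. The gap still falls on the outcome ranked first.

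Third, the Objective 2 section also mentions mixed models using the 9-month data and does not expressly confine them to the additional scores. Even if they were read as including the composite, no contrast with passive is named, and the passive arm is twice called descriptive.

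Some stronger readings are tempting but unsupported:

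- That the trial cannot say whether either intervention changed the score. The Descriptive analysis section gives means, SDs and confidence intervals by arm, and the randomised data exist. What is missing is a planned comparison.
- That the plan would usually miss a real meditation effect. Power depends on an unknown English effect. Section 1 also says that language learning has no known influence on emotion regulation, so a small English effect is plausible. A null would be reported as no difference from English, not as no effect.
- That the composite is more reliable than its components. No reliability figure is given.
- That the extra contrasts come from a model already fitted. The SAP's method for two groups is a t-test or Wilcoxon test.

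**Conclusion.** The mismatch is real and confined to this outcome. Objective 2 includes comparison with no intervention, and the SAP plans neither an estimate nor a test of it for the global composite or its subscores. The planned test remains valid for the question it asks, and no primary endpoint is affected.

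The practical size depends on how far English moves the score. Under the assumed +0.5 SD for meditation and 50 per arm, the planned test's power runs from about 17% to 70% as the English effect falls from +0.3 to 0 SD, against 70% for meditation versus passive at the same level. These are illustrations, without covariate adjustment or missing data. The mismatch itself is read from the text and needs no assumption. It should be corrected, because the passive-arm data are already part of the trial and the change is small.

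**What to change.** In the secondary SAP, under Behavioral outcomes, Type I error rate and Objective 2 (WP 1 to 6):

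1. Keep meditation versus English on the global composite as the main test at two-sided 5% and as the only gate to the subscores.
2. Add meditation versus passive and English versus passive on the 18-month change in the global composite as supportive secondary contrasts, each with an estimate and a 95% confidence interval.
3. Prespecify Holm over those two (2.5% for the smaller p-value, then 5%). State that this controls error within the pair and not jointly with the main test.
4. Replace both statements that the passive arm is only descriptive. If the sponsor prefers to keep them, say openly that Objective 2 does not extend to a comparison with passive control for this score.

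The Purpose section requires approval before analysis and database freezing. If the SAP is already locked, make the change as a dated, labelled amendment.

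The cost is a few lines of text, two additional secondary tests and slightly more analysis work. No new data are needed, and the main test and its alpha do not change.

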# 1. RATIONALE FOR THE TRIAL – WORKING HYPOTHESES

The number of people over the age of 65 (referred to as seniors in the following) is steadily increasing in Europe and is expected to rise from 86 million (18% of the population) to about 120 million (24%) in 2040 (Jané-Llopis and Gabilondo, 2008). As the incidence of health problems increases with age, this growth in the number of older people represents a major social and economic challenge for European societies. For example, more than 50% of older adults have sleep problems (Ohayon and Vecchierini, 2005), 10 to 15% suffer from depression (Barua et al., 2011), 7 to 10% develop dementia (Jané-Llopis and Gabilondo, 2008). These health problems are often chronic, require long-term care, and have a significant impact on the quality of life of the individuals, those around them, and on the society in which they live. In addition, these problems are increased by stress and negative emotions, interact with each other, and increase the risk of Alzheimer's disease (AD) (Norton et al., 2014). Numerous studies have shown the deleterious effect of stress on the hippocampus (Ricci et al., 2012), a brain structure important for memory and vulnerable during aging and implicated in AD mechanisms. Sleep disturbances could also accelerate the pathological process of AD (Ju et al., 2013) and each depressive symptom increases the risk of dementia by approximately 20% (Wilson et al., 2002).

This project is based on the premise **that mental training in stress and emotion regulation through meditation could reduce these effects and thus improve the well-being and mental health of seniors and delay AD or reduce the risk of AD**. Although research in this field is still recent, studies have shown encouraging effects in seniors. Notably, meditation is reported to be associated with improved cognitive abilities (mainly attention but also memory, which are the two most age-sensitive functions and the most frequently impaired in AD) (Gard et al., 2014; Marciniak et al., 2014; Newberg et al., 2014). Other studies have shown that meditation is also thought to be associated with reduced stress, anxiety, depression, insomnia, feelings of loneliness and social exclusion (Chen et al., 2012; Innes and Selfe, 2014), and cardiovascular risk (Schneider et al., 2012). Furthermore, related to the notion of neuroplasticity, neuroimaging studies have shown that meditation is not only associated with a change in brain activity pattern during practice but may also produce long-term structural and functional brain changes, particularly in frontal and limbic areas (Newberg et al., 2014; Slagter et al., 2011) (Fox et al., 2014; Marciniak et al., 2014; Tang et al., 2015) -known to be susceptible to aging and AD. Finally, recent studies have shown that meditation may increase telomerase activity that impacts aging and AD (Schutte and Malouff, 2014). However, these results need to be confirmed, strengthened, and refined; indeed, the populations studied are very heterogeneous, the size of the studies remains small, and very few studies include a comparison to another type of active intervention. In this trial, therefore, we propose to include an active intervention and to use a randomized allocation to control for potential selection and confounding biases in order to preserve the validity of the comparisons. We chose to use an active foreign language learning intervention (English) because 1) like meditation, this learning corresponds to mental training; 2) its organization can structurally resemble the meditation intervention (group sessions, daily practice with audio support, etc.); 3) a positive effect can be expected because foreign language learning is known to have a positive impact on cognitive functions and brain

structures sensitive to aging and AD (Mårtensson, J. et al., 2012). Finally, in addition to being useful as an active intervention for demonstrating specific effects, this intervention has its own interest because foreign language learning in older adults has never been studied within a randomized trial in older adults. Unlike the meditation intervention, foreign language learning is not known to have an impact on emotion regulation. The outcome measurements will be chosen to compare the relative impact of the two interventions based on a priori hypotheses (some related to these emotional factors, others not).

**Understanding of the neurocognitive mechanisms of meditation is still limited.** Meditation can be conceptualized as "a set of complex emotional and attentional regulation strategies developed for various purposes including the development of well-being and emotional balance" (Lutz et al., 2008). **Affective (emotional) and cognitive (attentional) control** are therefore the most likely mechanisms by which meditation could impact aging and AD. Specifically, meditation could enhance the control role of the midbrain structures and the executive network on structures involved in memory, emotion and immune system regulation. This would lead to better emotional and cognitive control, which in turn would be associated with improved mental and physical health.

**The overall aim of the present trial is to assess the effects of a mindfulness-compassion meditation practice on the well-being and mental health of older adults and to investigate the attentional and emotional mechanisms involved in these effects. To address these objectives, we will use two complementary approaches: 1) we will study the effects of a meditation intervention (versus no intervention and versus another intervention) over 18 months in non-meditating seniors and 2) we will compare data from expert meditating seniors to data from non-meditating seniors before the intervention.**

To measure well-being and mental health, we will perform a series of behavioural, psycho-emotional, biological and neuroimaging measurements in non-meditating seniors before and after the intervention as well as in long-time senior meditators (so-called experts). In these same expert meditators, the brain activity associated with specific meditative practices (mindfulness versus compassion) will be measured in order to obtain the "neural signature" of these two meditative practices. These neural signatures will allow us to better understand the mechanisms underlying the effects measured in the 18-month intervention. Both groups (non-expert seniors and expert meditators) will be included in the same study because of the close relationship between the analyses performed on one and the other group.

## ***1.1. Cognitive functions, psycho-affective measurements and lifestyle***

### **1.1.1. Effects of aging and Alzheimer's disease**

Cognitive decline is one of the biggest concerns for the older adults. Cognitive abilities such as memory, attention and executive functions are affected early in the aging process (Craik & Salthouse, 2008; Deary et al., 2009). A decline in these domains can create difficulties in daily life and is a risk factor for developing AD (Jessen et al., 2014; Landau et al., 2010). AD is characterized by greater

cognitive impairments than those associated with so-called "normal" aging, affecting a variety of cognitive functions. Episodic memory deficits are the first to be identified by these patients, and are most often the focus of their complaint and the concern that leads them to consult. Contrary to normal aging where memory deficits are generally compensated by indexing, indicating that they reflect more a decline in retrieval (probably related to the decline in executive functions), AD is characterized by so-called "authentic" disorders that affect the encoding of information in memory (Eustache et al., 2006). In AD, delayed recall is particularly sensitive, as is autobiographical memory (Eustache et al., 2006). In addition to episodic memory tests, verbal fluency tasks appear to be particularly effective in detecting AD in the earliest stages. Thus, in patients with mild cognitive deficits (called MCI for Mild Cognitive Impairment), performance in verbal fluency and autobiographical memory can predict progression to AD (Chételat et al., 2005). Executive functions (flexibility, inhibition) are also affected early in AD (Salmon and Bondi, 2009).

